##### Behavioral Intent

The behavioral intent to reduce the intake of added sugars will be measured using a list experiment approach. In Textbox 2, we present the 6 experiments and their list items. The control group will receive a list of 5 items, whereas the treatment group will receive the same list but with 1 additional sensitive item. The sensitive item covers the topics of natural versus added sugar, consumption of sugar-sweetened beverages, fresh fruit intake, reading of sugar content on package labels, teaspoons of sugar consumed per day, and home cooking.

We will assess whether participants are motivated (in lists 1, 3, and 4) or unmotivated (in lists 2, 5, and 6) to undertake the sensitive item. For example, in list 1, imagine that the control group selects an average of 2 out of the 5 items, and the participants in the treatment group select an average of 2.2 out of the 6 items. Holding all else equal, we conclude that the prevalence of participants who would cut their daily intake of sugar is 20%. The intention to restore one’s freedom will be present if there are higher scores for the *unmotivated* lists in the treatment group than the control group. The intention to reduce sugar intake will be present if there are higher scores for the *motivated* lists in the treatment group than the control group.

To avoid alerting the participant to the purpose of the list experiment and order effects, the 6 list experiments will be presented in random order. We designed the items to minimize ceiling and floor effects [42]. As described in the *Statistical Methods* section, we will use regression models to estimate the prevalence of each sensitive item [43]. These data will be used to assess objective 2.

List experiment items. Each list experiment will be preceded by the question “How many of the five/six statements do you agree with? We don’t want to know which ones, just answer how many. This week I feel motivated/unmotivated to...”

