## Introduction

### Background

Entertainment-education media can be an effective strategy for influencing health behaviors [1-3]. However, entertainment-education media face the same challenges as other traditional persuasion methods [4]. Persuasive health messages often fail to achieve the desired effect [5], and in some cases, may arouse the motivation to reject a message, a phenomenon known as reactance [6].

The theory of reactance comprises 4 elements [6]: (1) freedom, which individuals possess insofar as they are aware of it and can enact it; (2) threat to freedom, which involves any pressure on the individual, making it more difficult to enact that freedom; (3) reactance, which is the motivation to re-establish the freedom if that freedom is eliminated or threatened with elimination; and (4) direct restoration, which involves the freedom of the individual to perform a forbidden act. Research in this field has led to the development of several strategies to reduce reactance to health messages pertaining to littering [7], use of e-cigarettes [8], use of alcohol [9], and eating behaviors [10], among other health-related messages [11-16].

We are particularly interested in the effect of social authority on reactance to persuasive health messages. Our starting assumption is that an agent (human or otherwise) that delivers a health message possesses some influence or social authority [17]. For example, persons who have high social authority, such as experts or doctors, are often recruited to promote health messages [18-20]. However, research has shown that individuals may perceive health messages from experts as coercive, threatening, or having an ulterior motive [21], which could provoke reactance and negate the impact of the intervention [22,23].

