### Outcome Measures

#### Overview

We will measure primary and secondary outcomes. Primary outcomes are based on the intertwined process cognitive-affective model, as described by Dillard and Shen [5] and Zhang [32] (Figure 2). In this model, there are two antecedents to reactance: the strength of the threat to freedom and trait proneness to reactance. Reactance is conceptualized as a mediator between the antecedents of reactance and behavioral intent to promote health-related activities. It is an intertwined process consisting of a cognitive and affective component that can be an experience of hostile, aggressive, or angry feelings. Furthermore, attitudinal and behavioral intentions are the consequences of reactance. The assessment of behavioral intentions can also help measure the direct restoration of freedom, which involves performing forbidden behavior and restoring participants’ need for self-determination and control [33]. In addition, source appraisal, which refers to the perception of the message source, is another important outcome of reactance [34].

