**List 2: Sugar-Sweetened Beverages**
This week I feel unmotivated to...wash my hands frequently.spend time watching movies.clean the toilets in my home.smoke marijuana.clip my toenails.reduce the amount of sugar-sweetened beverages I drink (sensitive item).

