**List 5: Teaspoons of Sugar**
This week I feel unmotivated to...clean my dishes after use.spend time on the internet.try learning a new language.play a prank on my partner.visit a car sales website.count how many teaspoons of added sugar I eat each day (sensitive item).

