**List 6: Home Cooking**
This week I feel unmotivated to...stock up on household supplies for a month.spend time gardening by myself.plan my next holiday.take a web-based course.go out with my friends.cook with fresh, whole foods (sensitive item).

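### A positive list difference on the *unmotivated* lists shows only lack of motivation, but the protocol reads it as an intention to restore freedom

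*Protocol article*

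**What the plan says.** The Background section names direct restoration as one of four elements of reactance theory: "direct restoration, which involves the freedom of the individual to perform a forbidden act". The Outcome Measures overview repeats the link to the act, "direct restoration of freedom, which involves performing forbidden behavior", and says that behavioral intentions can help to measure it.

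The Behavioral Intent section then sets the rule: "The intention to restore one’s freedom will be present if there are higher scores" for the *unmotivated* lists in the treatment group than in the control group. Trial Design and Behavioral Intent both define these groups as the six-item and five-item lists within a video arm, not as video arms.

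The *unmotivated* lists are 2, 5 and 6. Their sensitive items are "reduce the amount of sugar-sweetened beverages I drink (sensitive item"), "count how many teaspoons of added sugar I eat each day (sensitive item") and "cook with fresh, whole foods (sensitive item"). The section assigns the list data to objective 2.

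**The concern.** Feeling unmotivated to do a recommended task is not the same as intending to do what the message discourages. Someone may not want to count teaspoons because it is tedious. Someone who drinks no sweetened beverages may truthfully feel unmotivated to reduce them, and the eligibility criteria do not exclude such people. Under the stated rule, both count towards restoring freedom.

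The rule also needs no comparison between videos. It is applied to the list difference inside an arm, so it can be met where there was no sugar message to resist. Behavioral intent is listed among the primary outcomes, so a statement that viewers intended to restore their freedom would be a reported conclusion of the trial.

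**Working it through.** **1. What the items ask, against what restoration means.** Background and the overview tie direct restoration to performing the forbidden act or behavior, which for this message is consuming added sugar. The six sensitive items in Textbox 2 are:

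| List | Stem | Sensitive item | Asks about consuming sugar? |
|---|---|---|---|
| 1 | motivated | cutting added sugar | no |
| 2 | unmotivated | reducing sweetened drinks | no |
| 3 | motivated | eating fruit | no |
| 4 | motivated | checking labels | no |
| 5 | unmotivated | counting teaspoons | no |
| 6 | unmotivated | cooking with fresh foods | no |

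None of the control items asks about it either.

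**2. What the list difference estimates.** The protocol's own example for list 1 is 2.2 − 2.0 = 0.20, read as a prevalence of 20%. This reproduces. Statistical Methods uses the same estimator within each arm. Applied to an *unmotivated* list, it estimates the share who agree that they are unmotivated. Under the usual list-experiment assumptions (truthful answers, and control-item answers unchanged by the added item) its expected value is a proportion, so it is zero or more in every arm. The motivated and unmotivated rules can therefore both be met in one arm.

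**3. How easily the within-arm rule is met.** Inputs:
- Standard deviations 0.85 and 1.0, from Sample Size.
- 4000 / 5 arms / 2 lists = 400 per list per arm, from Sample Size and Trial Design.
- True share unmotivated, p. The protocol gives no figure, so a range is assumed.

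Standard error of one list difference: √((0.85² + 1.0²)/400) = √(1.7225/400) = 0.0656.

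Chance that the six-item mean is higher: Φ(p/0.0656). Chance that it is also significant at the two-sided 5% level: Φ(p/0.0656 − 1.96).

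| Assumed p | p/SE | Higher mean | Significantly higher |
|---|---|---|---|
| 5% | 0.76 | 78% | 12% |
| 10% | 1.52 | 94% | 33% |
| 15% | 2.29 | 99% | 63% |
| 20% | 3.05 | 99.9% | 86% |
| 30% | 4.57 | >99.9% | 99.5% |

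**4. The earthquake arm.** These figures do not depend on which video was shown. According to the section on choice of comparators, the earthquake video has no health or sugar content. Strengths and Limitations expects it to arouse very little state reactance or none. The rule as written would still usually declare an intention to restore freedom there.

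**5. The between-arm contrast.** The interaction in the regression model subtracts one arm's list difference from another's, so disinterest common to both arms cancels. Its standard error is √2 × 0.0656 = 0.0928. What remains is a difference in the share unmotivated, which is still not an intention to consume sugar.

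**The case against.** Much of the case on the other side stands.

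- **Reactance has its own measure.** The Psychological Reactance section defines it by the anger and negative-cognition items, and those data serve objective 1. A reader might infer that disinterest will be reported as reactance, or that the trial's null hypothesis is compromised. The protocol does not support that, because list counts do not enter the reactance scale.
- **The wording is looser than a flat contradiction.** The rule speaks of an intention to restore freedom, and Background defines "reactance, which is the motivation to re-establish the freedom if that freedom is eliminated or threatened with elimination", which is close to that phrase. The overview says only that intentions can help to measure direct restoration. However, the Behavioral Intent section drops that hedge and makes the finding categorical, and the items do not measure a motivation to regain freedom either.
- **List 2 is a partial proxy.** For someone who drinks sweetened beverages, being unmotivated to reduce them is close to declining to change. A reader might infer that restoration requires eating more sugar, or that the three lists say nothing about it. The protocol's definitions require the act, not an increase in it. The mismatch is plainest for lists 5 and 6.
- **The planned model compares arms.** The interaction removes baseline disinterest, and the three sugar videos differ only in narrator, so general dullness is largely shared among them. This protects the estimates. It does not rescue the rule, which is stated on the list difference within an arm.

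Nor can the rule be excused as a detail left to a fuller document. It is stated outright, and the article calls itself the full protocol.

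**Conclusion.** The point holds for one interpretive rule. A positive difference on lists 2, 5 and 6 supports a statement about lack of motivation and nothing more. It does not show an intention to restore freedom, and direct restoration as the protocol defines it is not asked about in any of the six lists. Taken literally, the rule would be met by ordinary disinterest with probability 78% at an assumed 5% prevalence and at least 94% from 10% upward, in any arm. If statistical significance were required, the range is 12% at 5% prevalence to 99.5% at 30%.

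These probabilities rest on assumed prevalences, a normal approximation, the planning standard deviations held fixed, complete data at 4000 participants, and the usual list-experiment assumptions. The share of participants who would be misread cannot be derived from the protocol. No estimate or test changes, and the reactance scale and objective 1 are untouched. What changes is the conclusion that may be drawn from the behavioral-intent outcome under objective 2.

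**What to change.** 1. Delete the sentence in Behavioral Intent that equates higher *unmotivated* scores with an intention to restore freedom, and make no such claim in the results.
2. Report lists 2, 5 and 6 within each arm as the prevalence of lack of motivation for the named behavior.
3. Interpret any effect of the message only through the between-arm VideoArm × TreatList contrast already specified in Statistical Methods, and describe it as message-related loss of motivation.
4. State that direct restoration was not measured.

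The cost is a narrower claim. The analysis itself is unchanged, since the interaction is already planned, although that contrast is less precise than a single list difference (standard error 0.0928 against 0.0656). Replacing a list item with one on the act itself is no longer possible for this trial, because data collection was completed in December 2020.

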## Methods

### Trial Design

This study consists of a parallel group RCT. Participants will be randomized to 1 of 5 arms: either the same sugar-intervention video narrated by a preadolescent daughter (arm 1: low social authority), the daughter’s mother (arm 2: equivalent social authority), or a family physician (arm 3: high social authority), or a content placebo video with a health message about tanning and sunscreen (arm 4: no sugar message), or a placebo video about earthquakes (arm 5: no sugar or health message). We will randomize the participants in a 1:1:1:1:1 ratio to the trial arms. Participants will watch 1 video once from start to finish.

Nested in each of the five trial arms is a list experiment. For each list experiment, participants will be randomized at a 1:1 ratio to a control or treatment group. The control group will receive a list of 5 items about behavioral intent (unrelated to sugar consumption). The treatment group will receive the same 5 items and a sensitive item about behavioral intent to reduce sugar intake. We will use the list experiment to reduce social desirability bias, as participants may already be primed to answer favorably to questions about sugar consumption.

At the end of the study, participants assigned to the content placebo (*arm 4*) or placebo (*arm 5*) will be given a choice to watch the video intervention. Their choices will be recorded. Participants who choose to watch will be randomized at a 1:1:1 ratio to the sugar video narrated by the daughter, mother, or physician. The complete trial flowchart is presented in Figure 1.

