### Statistical Methods

#### Statistical Methods for Primary and Secondary Outcomes

For the descriptive statistics, we will obtain means and SDs of age, sex, country of residence, and education status variables. We will use an analysis of variance to estimate pairwise differences in means between the sugar-intervention videos, content placebo video, and placebo video. We will use the Tukey range method to create confidence intervals for all pairwise differences between the means while controlling for the family error rate. Within each trial arm, we will estimate the prevalence of behavioral intent as the difference between the treatment and control list for each list experiment. From these estimates, we will obtain the differences in means between trial arms. This approach is analogous to a difference-in-difference analysis, which we will implement by specifying the main and interaction terms in an ordinary least squares (OLS) regression model. The OLS equation for each list experiment is given as follows:

y = b_0_ + b_1_*VideoArm* + b_2_*TreatList* + b_3_*VideoArm* × *TreatList*

where y is the number of statements in the list that the participant agreed with, *VideoArm* indicates the arm to which the participant was assigned, and *TreatList* indicates if the participant was assigned to the treatment list within that arm. We will calculate standard errors, 95% CIs, and *P* values for linear combinations of coefficients from the OLS model. We will use R statistical software to perform the analysis.

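### The rule for declaring freedom restoration rests on a within-arm list difference, which is only the prevalence of the sensitive item and cannot show a reaction to a video

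*Protocol article*

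**What the plan says.** The Behavioral Intent section of the protocol article defines its two groups by list length: "The control group will receive a list of 5 items, whereas the treatment group will receive the same list but with 1 additional sensitive item". Its worked example has a control mean of 2 and a treatment mean of 2.2 on list 1, from which "we conclude that the prevalence of participants who would cut their daily intake of sugar is 20" per cent.

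Two decision sentences follow. The one on restoration, for the unmotivated lists (2, 5 and 6), says: "freedom will be present if there are higher scores for the *unmotivated* lists in the treatment group than the control group". The one for the motivated lists (1, 3 and 4), with the 5-item group again as comparator, says: "The intention to reduce sugar intake will be present if there are higher scores for the *motivated* lists in the treatment group than the control". Neither sentence sets a threshold, names a test or refers to a comparison between videos.

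Under Trial Design, "Nested in each of the five trial arms is a list experiment", so the lists are also given after the earthquake video. There, too, "For each list experiment, participants will be randomized at a 1:1 ratio to a control or treatment group".

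Statistical Methods takes a further step. It estimates the list difference within each arm, and then: "From these estimates, we will obtain the differences in means between trial arms". The tool is an OLS model with a VideoArm × TreatList interaction. Explanation for the Choice of Comparators likewise attributes effects to a video through differences between arms.

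**The concern.** The treatment list is the control list plus one item. If the extra item does not alter the answers to the other five, the expected difference between the lists equals the proportion who endorse that item. A proportion is never negative, so any endorsement at all satisfies the rule in expectation.

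For the unmotivated lists this matters because the label claims more than a prevalence. A participant may have no wish to count teaspoons of sugar, or to change what they drink, without having seen any message. The article's model makes behavioral intention a consequence of reactance, and it defines restoration as a response to a threatened freedom. Strengths and Limitations expects the earthquake video to arouse little or no reactance. Yet the rule, applied in that arm, would call ordinary unwillingness the restoration of freedom. Behavioral intent is listed among the primary outcomes, so a wrong label here would produce a wrong statement about a boomerang effect.

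**Working it through.** **Inputs**
- SDs of the list counts: 0.85 (control list) and 1.0 (treatment list), from Sample Size.
- Participants per list cell: 4000 ÷ 5 arms ÷ 2 lists = 400, from Sample Size and Trial Design.
- Baseline prevalence p of an unmotivated sensitive item in the earthquake arm: not given. It is an assumption here, shown over a range. For orientation, the planning means of 2.0 and 2.15 in Sample Size differ by 0.15.

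**The plan's own figure.** A mean of 2.2 less a mean of 2.0 gives 0.20, read as 20%. This reproduces, and it confirms that the list difference is a prevalence estimate.

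**The rule within one arm, one list**

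SE = √((0.85² + 1.0²) ÷ 400) = √(1.7225 ÷ 400) = 0.0656

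P(treatment list higher) = Φ(p ÷ SE)

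P(higher and significant at two-sided 5%) = Φ(p ÷ SE − 1.96)

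| Assumed p | Treatment list higher | Also significant |
|---|---|---|
| 0% | 50% | 2.5% |
| 1% | 56% | 3.5% |
| 5% | 78% | 12% |
| 10% | 94% | 33% |
| 15% | 99% | 63% |
| 20% | 99.9% | 86% |
| 30% | about 100% | 99.5% |

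The rule speaks of lists in the plural. If all three unmotivated lists had to point the same way, and they are treated as independent with equal p, the probability is the cube of the single-list value: 47% at 5%, 82% at 10%, 97% at 15% and 99.7% at 20%. The same participants answer all six lists, so independence is only an approximation.

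**The between-arm contrast**

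SE of the difference between two arms' list differences = √2 × 0.0656 = 0.0928

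In a simulation with equal prevalence in a sugar arm and the earthquake arm (20,000 runs at each of 5%, 10%, 20% and 30%), the contrast was significant at two-sided 5% in 4.8% to 5.2% of runs. In the same runs the sign rule was met in both arms in 87% at p = 10% and 99.8% at p = 20%. The interaction thus holds its error rate whatever the baseline, and the sign rule does not.

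Power of the contrast for a 15-point difference on one list, two-sided 5% without adjustment: the ratio 0.15 ÷ 0.0928 = 1.62, and Φ(1.62 minus 1.96) = 37%. Difference detectable with 80% power: 1.96 plus 0.84 is 2.80, and 2.80 × 0.0928 = 0.26, or 26 points.

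**The case against.** The best reply is that the rule is not the analysis. Behavioral Intent describes how to read a list difference and then refers to Statistical Methods, where the arm-by-list interaction is specified. Explanation for the Choice of Comparators defines the content, health awareness and total intervention effects as differences between videos. Nowhere does the article say that effectiveness will be concluded from a list difference inside one arm. This stands, and it limits the point. A reader might infer that objective 2 is bound to be answered wrongly; the documents do not support that.

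Three other strong readings also fail.
- The sentence on intention to reduce sugar can be read as a plain prevalence statement. If some earthquake viewers intend to cut sugar, that intention is indeed present among them, and it is the baseline that the interaction subtracts.
- Meeting both rules in one arm is no contradiction, because the motivated and unmotivated lists carry different sensitive items. A person can want to eat fruit and not want to count teaspoons.
- A false restoration rate near 100% cannot be claimed outright. It depends on a baseline that the documents do not give, and at 1% to 5% the sign rule is met on one list in only 56% to 78% of cases.

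What the reply does not remove is the restoration label. The Behavioral Intent section is the only place that says what counts as restoration, and it does not tie that conclusion to the interaction. Reading treatment and control as video arms would rescue the sentence, but the same section has just defined them as list groups.

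**Conclusion.** The concern holds for one interpretive rule. As written, the restoration criterion is a statement about prevalence and cannot tell a reaction to a video from unwillingness that existed before it. In the no-message arm, on one list, a higher treatment-list mean alone would be found with probability about 78%, 94%, 99% and 99.9% at assumed baselines of 5%, 10%, 15% and 20%. If significance within the arm were also required, the figures are about 12%, 33%, 63% and 86%.

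These results rest on the plan's SDs, 400 per list cell, a normal approximation, truthful answers, and no influence of the extra item on the other five. The baseline values are assumptions. The planned model is sound for this purpose; the fault is that the stated criterion does not use it.

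**What to change.** Rewrite the two decision sentences in Behavioral Intent.
- Report list differences within an arm only as prevalences of the sensitive item.
- Conclude freedom restoration only when the list difference on an unmotivated list is higher in a sugar arm than in arm 5 (or arm 4), using the VideoArm × TreatList contrasts with their confidence intervals. With five arms, b3 stands for a set of contrasts, so name the reference arm.
- State any effect of a video on intention to reduce sugar as the corresponding between-arm contrast on the motivated lists, and keep the pairwise comparisons among arms 1 to 3.
- Say whether one unmotivated list suffices or how the three are taken together, since the criterion needs this to be usable.

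The change needs no new data and no new model. The Results section reports that data collection and analysis are complete, so the correction should govern how the results are interpreted and should be disclosed as a clarification.

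The cost is less favourable conclusions. Per list, the interaction has a standard error of about 0.093 against 0.066 within an arm. With about 37% power for a 15-point difference, a null contrast should be reported with its interval and not as evidence that no restoration occurred.
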